
### Statistical methods for primary and secondary outcomes

#### Analysis for aim 1: Identify practice capacity for the adoption of TASSH in CHPS zones and develop a culturally tailored PF strategy using qualitative methods

The semi-structured interviews and user-testing interviews will be transcribed and entered into NVivo, version 11, for data analysis. We will use the framework approach to qualitative data analysis [40], a five-step process that involves the following: (i) familiarization (a process during which the researcher becomes immersed in the details of multiple sources of data to gain a general understanding of the content and to document initial impressions), (ii) developing a theoretical framework (a process by which the researcher identifies emergent themes in the multiple sources of data using existing theories as a guide [40]; these themes will be continually refined and compared to each other), (iii) indexing (during which the researcher becomes further immersed in the data in order to refine identified themes and subthemes), (iv) summarizing data in an analytical framework (during which the researcher reduces materials into understandable, but brief summaries of what was said by stakeholders), and (v) data synthesis and interpretation (which allows for comparison of themes and subthemes against original transcripts, field notes, and audio recordings to ensure appropriate context [40]). Following the framework approach, as described above, the data will be independently coded by the two-three research members to reduce the potential for bias. Inter-rater reliability will be determined based on a subset of the data, for example, the interviews, and will be repeated until satisfactory agreement among raters is achieved (i.e., 80% of coded data). Discrepancies in coded data will be resolved by consensus. After systematically reading all transcripts, they will be coded into concepts reflecting the aim of this phase. For example, responses will be coded according to provider-level factors (e.g., knowledge of TASSH toolkit) and issues related to practice capacity with using the TASSH toolkit in CHPS (e.g., logistics/resources involved). Established procedures to enhance the trustworthiness of our analysis will be used [41], including analyses of codes that do not fit our coding scheme, development of an audit trail documenting analytical decisions, and member-checking presentations to the Steering Committee. The identified concepts will then be grouped into categories, and themes uniting the categories will be determined. A detailed analysis of the interviews should generate a conceptual model that elucidates barriers to the uptake of the TASSH toolkit within the CHPS compounds and modified PF strategy tailored to the CHPS context to overcome these challenges.

#### Analysis for aim 2a: The adoption of TASSH will be higher in the CHPS compounds randomized to the PF strategy than those in usual care at 12 months post-randomization

This analysis will be accomplished with a multilevel mixed model using an unstructured covariance matrix across two time points, baseline and 12 months. The analysis will have one within-person factor—time (baseline and 12 months coded naturally as months 0 and 12)—and one primary between-patient factor (randomization group dummy coded as 0 = UC and 1 = PF). Fixed effects will be specified for time, randomization group, and their interaction effect (group by time). The outcome measure will be a composite index for adoption of TASSH (defined as rate of identification of HTN, rate of lifestyle counseling for patients with HTN, and medication referral for patients with HTN). Additionally, the CHOs will be nested within compounds creating a 3-level analytic model (observations nested within CHOs nested within compounds). Random effects will be specified for CHPS and for CHO, adjusting for the clustering of measures within CHO and CHO within CHPS. Multilevel modeling software (SAS, version 9, PROC MIXED) will be used to compute full information maximum likelihood (FIML) estimates of the model parameters. The PROC MIXED procedure will use an error structure that allows for the possibility of group differences in (a) the error variances at 12 months and (b) the serial correlations of the baseline with the 12-month outcomes. The primary test is the group × time interaction, and the resulting *F* test will provide the primary “intent to treat” test of the hypothesis. If this is statistically significant at the two-tailed *α* = .05 level, for ease of interpretation, we will estimate and report the magnitude of the treatment effect, with 95% CI for adoption. Ideally, the randomization of participants to treatment groups will obviate the need for any covariates in the analysis. However, in the event that baseline differences between the patients in each group on the outcomes, demographic, or secondary measures are found, those variables will be included as covariates in the model (including their interactions with time).

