#### Sample size and power estimates

The proposed design is a cluster randomized design to compare PF versus usual care. The primary outcome is a composite measure of adoption ratings to assess the degree to which the TASSH protocol is implemented at the CHPS compounds. The secondary outcomes are the difference in the change in systolic BP between patients at the CHPS sites randomized to PF versus those at the usual care CHPS sites. The unit of randomization is the CHPS compound, and the total sample size is the average number of CHOs at the CHPS sites who will provide the adoption ratings (primary outcome) at each site × the number of CHPS compounds and the average number of patients whose systolic BP will be assessed (secondary outcome) enrolled at each CHPS compound × the number of CHPS compounds. In order to estimate the number of CHPS compounds and the average number of CHOs and the average number of patients needed to have power of .80 for a hypothesis test with a type 1 error rate (alpha) of .05, we have assumed a moderate standardized effect size (*d*) of .50 of the difference in change in adoption ratings between the CHOs in the CHPS sites in the UC group versus those in the CHPS sites in the PF group from baseline to 12 months. We note that Baskerville et al. reported in a systematic review of practice facilitation in primary care settings an average effect size of *d* = .56 [15]. We also calculated the sample size for an assumed degree of dependency (intra-cluster correlation—ICC) of the CHOs’ data within CHPS compounds of .10. Thus, for an ICC of .10 and 2 CHOs providing the adoption ratings, our target number of CHPS compounds to recruit is 70. As such, a total of 140 CHOs will participate in this study. For the secondary outcome of patient change in systolic BP, we will have substantially greater power than .80 under the same effect size (*d* = .50) and ICC assumptions as we anticipate enrolling an average of 10 patients/compound. So, with 70 compounds, we would enroll 700 patients. Aim 3 concerns the correlation relationship between different mechanisms of change and the change in adoption ratings between baseline and 12 months. For this analysis, we will have the entire sample of 70 compounds and 140 nurses. With this sample and the same assumptions that we made for aim 2a and aim 2b, we will have power of .80 to detect a moderate correlation of .30. Finally, aim 4 concerns detecting a quadratic pattern consistent with sustainability across the baseline and 12- and 24-month time points. Again, the entire sample will be available for this analysis. The standardized effect size for the quadratic effect will depend considerably on the exact form of the quadratic pattern. The largest effect size would occur when the adoption is not sustained; that is when the adoption ratings revert to their baseline values after PF has ended. With the proposed sample size, we will have power greater than .90 to determine if this unwelcome event occurs.

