#### Analysis for aim 2b: Mean systolic BP will be lower among patients in the CHPS compounds randomized to the PF strategy than those in usual care at 12 months post-randomization

This analysis will be accomplished using a similar analytic strategy as described for the quantitative analysis for aim 2a. However, in this analysis, the measurements will be taken at the level of the patient rather than the CHO. We will specify a generalized linear multilevel mixed model with fixed effects for time, intervention, and intervention by time. Random effects will be specified for CHPS, CHO, and patient, accounting for measurements clustered within patient, patients clustered within CHO, and CHOs clustered within CHPS. SBP will be measured as a continuous variable in mmHg at baseline and 12 months for all patients. Multilevel modeling software (SAS, version 9, PROC MIXED) will be used to compute full information maximum likelihood (FIML) estimates of the model parameters for the fixed and random effects.

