#### Analysis for aim 3: Sustainability of TASSH will be higher at the CHPS zones randomized to PF than those in CHPS zones randomized to usual care at 24 months post-randomization

Sustainability will be defined as adoption of TASSH at 24 months (12 months following the completion of the intervention). As in aim 2a, this analysis will be conducted at the level of the CHO. The analysis will be accomplished with a multilevel mixed model using an unstructured covariance matrix across two time points, baseline and 24 months post-randomization. Fixed effects will be specified for time, group, and group by time. Random effects will be specified for CHO and CHPS to account for the clustering of measurements.

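### No compound-by-time random effect is stated, so as naturally read the group-by-time tests ignore clustering of change: serious for systolic BP, small for the primary outcome

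*Protocol article*

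**What the plan says.** **Aim 2a (primary).** The model is a three-level mixed model "using an unstructured covariance matrix across two time points, baseline and 12 months", with fixed effects for time, group and their interaction. The interaction is named as the primary test, and its significance is judged as follows: "If this is statistically significant at the two-tailed *α* = .05 level". On clustering the section says: "Random effects will be specified for CHPS and for CHO, adjusting for the clustering of measures within CHO and CHO within CHPS". A separate sentence describes a PROC MIXED error structure whose 12-month variance and serial correlation may differ by group.

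**Aim 2b (systolic BP).** A similar strategy at patient level: "Random effects will be specified for CHPS, CHO, and patient, accounting for measurements clustered within patient". Systolic BP enters at baseline and 12 months.

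**Aim 3 (sustainability).** The same CHO-level model with baseline and 24 months: "Random effects will be specified for CHO and CHPS to account for the clustering of measurements".

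**Sample size and power estimates.** The effect is defined on change: "we have assumed a moderate standardized effect size (*d*) of .50 of the difference in change in adoption ratings". The number of compounds follows from clustering: "Thus, for an ICC of .10 and 2 CHOs providing the adoption ratings". The same effect size and ICC are then carried over to change in systolic BP, with about 10 patients per compound.

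**The concern.** With two time points, the group-by-time interaction is the difference between arms in mean change. A compound effect that is the same at both times disappears when change is formed. To carry clustering into this test, the model needs a term that lets compounds differ in how much they change. None of the three analyses names one.

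Compounds are the unit of randomisation, and the trial is sized on the premise that changes within a compound are correlated. If the analysis treats those changes as independent, standard errors are too small, confidence intervals too narrow, and the 5% level is not held. The effect grows with the number of people per compound. It therefore falls mainly on systolic BP, the trial's clinical-effectiveness comparison.

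**Working it through.** **Inputs.** From the sample size section: power and alpha ("power of .80 for a hypothesis test with a type 1 error rate (alpha) of .05"), d = .50 on change, ICC .10, 2 CHOs and about 10 patients per compound, 70 compounds. From the aim 2a analysis: a two-sided test. From the masking section: 35 compounds per arm.

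**Step 1: reproduce the plan's figure.**
- Unclustered size per arm: 2 × ((1.96 + 0.84)/0.50)² = 62.8 CHOs.
- Design effect for 2 CHOs: 1 + (2 − 1) × .10 = 1.10.
- 62.8 × 1.10 = 69.1 CHOs per arm, or 34.5 compounds, rounded to 35 per arm and 70 in all. This agrees with the plan.
- Without the design effect, 62.8/2 = 31.4, which rounds to 32 per arm and 64 in all. The stated 70 thus fits an ICC of .10 applied to change.

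**Step 2: what a random intercept does to the test.** For compound i, person j and time t, write

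Y = fixed part + u(i) + v(ij) + e(ijt).

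The change from baseline is the fixed part of change + e(ij,12) − e(ij,0). Both u(i) and v(ij) have gone. A compound-by-time term w(it) would leave w(i,12) − w(i,0), which is shared by everyone in the compound and is the clustering of change.

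As a numerical check, three data sets with compound-level variation in change (2 people per compound) were fitted by maximum likelihood with compound and person intercepts. Each time the interaction estimate equalled the raw difference in mean change. Its standard error equalled the unclustered one to four decimals (0.1679, 0.1648 and 0.1599 from both routes). The optimiser gave convergence and boundary warnings, but the results match the algebra.

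**Step 3: size of the error.** With m people per compound and ICC ρ of change, DE = 1 + (m − 1)ρ. The standard error is too small by 1 − 1/√DE, and the true two-sided level is 2 × (1 − Φ(1.96/√DE)).

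- Systolic BP, m = 10, ρ = .10: DE = 1.90; shortfall 1 − 1/1.378 = 27%; level 2 × (1 − Φ(1.422)) = 15.5%.
- Primary, m = 2, ρ = .10: DE = 1.10; shortfall 1 − 1/1.049 = 5%; level 2 × (1 − Φ(1.869)) = 6.2%.

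| ICC of change | Primary (m = 2) | Systolic BP (m = 10) |
|---|---|---|
| 0 | 5.0% | 5.0% |
| .01 | 5.1% | 6.1% |
| .05 | 5.6% | 10.4% |
| .10 (plan) | 6.2% | 15.5% |
| .20 | 7.4% | 24.2% |

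Only the .10 row uses the plan's value; the others show the range. Aim 3 has the same structure as the primary analysis, so its figures are those for m = 2.

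A simulation of 40,000 trials with 35 + 35 compounds and ICC .10 gave 6.3% (m = 2) and 15.7% (m = 10) when clustering of change was ignored. A test on compound mean changes with 68 degrees of freedom gave 5.1% in both cases.

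**Step 4: power once clustering is counted.** For the primary outcome, 0.50/√(2 × 1.10/70) = 2.82. Power is .805 by the normal approximation and .794 by t with 68 degrees of freedom.

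**The case against.** The strongest reply is that the article never says the effects are intercepts only. It says random effects, without their form, and gives no level for the unstructured matrix over time. That matrix could sit at compound level, with the separately described error structure as the residual part. The form of random effects and the degrees-of-freedom method are ordinary content for an analysis plan that is not shown, and the sample size shows that clustering was meant to be counted.

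Part of this stands. A reader might infer that the protocol fixes an intercept-only model. It does not, and a compound-level matrix is not excluded. But intercepts are the natural reading:
- In aim 2b the patient effect can only be an intercept. Two readings per patient give three moments, whereas intercept variance, slope variance, their covariance and a residual make four parameters. CHPS and CHO are listed in parallel with patient, and nothing marks them as different.
- In aim 2a the variances and serial correlation over time are described as part of the error structure.
- The article goes beyond leaving detail open. It fixes the random effects, estimator, software and test, and says that these effects adjust for clustering.

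Three other strong readings are not supported:
- **The primary test is affected as badly as systolic BP.** With 2 CHOs per compound it moves only from 5% to about 6.2%.
- **The aim 2a model fails because a CHO intercept is redundant beside an unstructured within-CHO matrix.** If the matrix is at that level, the intercept is indeed redundant, but it is absorbed and leaves the test unchanged.
- **Inflation is certain.** The .10 is a planning value for the CHOs' data, extended to patients by the same section. With no between-compound variation in change, nothing is inflated.

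**Conclusion.** The point holds in conditional form. As naturally read, the models for aims 2a, 2b and 3 do not carry into the group-by-time test the clustering of change for which the trial was sized. At the plan's ICC of .10 the type I error is about 15.5% for systolic BP, which is serious, and about 6.2% for the primary outcome, which is small. Systolic BP is still at about 10% if the ICC is half the planned value.

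The figures assume complete data and equal compound sizes, apply the ICC of .10 to change, and ignore any extra clustering of patients' changes within a CHO. The sample size itself is not in question.

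**What to change.** - In aims 2a, 2b and 3, specify a compound-by-time random effect, or an unstructured covariance over time at compound level. Test group by time with compound-level denominator degrees of freedom, about 70 − 2 = 68.
- State the level of the unstructured matrix. Where it is within CHO, omit the CHO intercept. This is a coding matter that does not change the test.
- REML with Kenward-Roger degrees of freedom is a reasonable refinement, not essential. A model of the 12-month value on baseline with a compound effect is an alternative, not an equivalent: it conditions on baseline and, fitted simply, drops people who lack either value, whereas the missing-data section keeps everyone enrolled.

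**Cost.** A line or so of model code per analysis, matching text, and no new data. At ICC .10 the confidence intervals widen by about √1.90 − 1 = 38% for systolic BP and √1.10 − 1 = 5% for the primary outcome, compared with intervals that ignore clustering of change. Primary power stays at about .79 to .80 with 70 compounds. For systolic BP at d = .50 it stays above .99 (350/1.90 = 184 effective patients per arm).

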## Trial status

The study-specific manual of operations and policies has been developed. The first cohort (18 CHPS zones) has been randomized and enrolled. Also, 72 CHOs from the 36 zones have been trained to start implementation. The Data Safety and Monitoring Board has been formed and has already had its first meeting which was held on 2 July 2019. Steering Committees have been constituted and already had 4 meetings. The pre-implementation activities and contextual assessment of aim 1 have been completed. Enrolment into the trial started in November 2019 and should be completed by July 2021. This is study protocol version 4.0, and the version date is August 21, 2019.

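### The primary analysis picks covariates from observed baseline differences, with no list or threshold, and estimates the effect and its 95% CI only if the test is significant

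*Protocol article*

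**What the plan says.** The protocol article, under the analysis for aim 2a, fits a mixed model in which baseline and month 12 are both responses, with an unstructured covariance. The primary test is the group by time interaction. Two rules follow.

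- Covariates: randomisation should make them unnecessary. The exception applies "in the event that baseline differences between the patients in each group on the outcomes, demographic, or secondary measures are found". What happens in that case is also laid down: "those variables will be included as covariates in the model (including their interactions with time").
- Reporting: the condition opens with "If this is statistically significant at the two-tailed" and sets alpha at .05. Once it is met, the plan is this: "for ease of interpretation, we will estimate and report the magnitude of the treatment effect, with 95% CI for adoption".

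No other section names a covariate set, defines when a difference counts as found, or promises an estimate after a non-significant test. The analysis plan is not shown and may add detail. These are nevertheless rules that the protocol states, not gaps left for a later document.

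**The concern.** The covariate rule means that the primary model is known only after the arms have been compared at baseline. In a randomised trial such differences arise by chance (at the level of the compounds), so they are a poor guide to what deserves adjustment; the guide should be how strongly a variable predicts the outcome. Because the word found has no definition, two analysts could follow the rule and fit different primary models.

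The rule also fits the model badly. It compares patients, but the aim 2a observations belong to CHOs nested in compounds. It lists the outcomes among the candidates, although the baseline outcome is already a response in the model.

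Under the reporting rule, a non-significant primary result would come without an interval. Readers could not tell a trial that excludes a useful effect of practice facilitation (PF) over usual care (UC) from one that is merely imprecise.

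**Working it through.** 1. **The plan's own figure.** Inputs from the section on sample size and power: "power of .80 for a hypothesis test with a type 1 error rate (alpha) of .05", d "of .50 of the difference in change in adoption ratings between the CHOs", ICC .10, 2 CHOs per compound. CHOs per arm without clustering: 2 × (1.960 + 0.842)² / 0.50² = 62.8, so 63. Design effect: 1 + (2 − 1) × 0.10 = 1.10. 63 × 1.10 = 69.3, so 70 CHOs per arm, which is 35 compounds per arm and 70 in all. The stated figure reproduces. Power with 70 CHOs per arm is 0.805 (normal) or 0.794 (t, 68 df).

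2. **How often the covariate rule would act by chance.** Assume a difference means p < 0.05 and the variables are independent (the protocol gives neither the test nor the number). The chance of at least one flag is 1 − 0.95^k: 23% for k = 5, 40% for k = 10, 64% for k = 20. This is how often the model would change, not an error rate.

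3. **Type I error and power.** Simulation of 35 + 35 compounds with 2 CHOs each, ICC 0.10 and 8,000 runs per setting (Monte Carlo error about 0.002 at 5%). The baseline to 12-month correlation ρ is assumed. The rule was applied to the baseline score alone: adjust by ANCOVA if the baseline test has p < 0.05, otherwise test the change. The last column takes the smaller p-value of the two models every time. Power is at d = 0.50 SD of change.

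| ρ | Change test: type I, power | ANCOVA always: type I, power | Rule: type I, power | Free choice: type I |
|---|---|---|---|---|
| 0.3 | 0.049, 0.79 | 0.050, 0.93 | 0.041, 0.81 | 0.077 |
| 0.5 | 0.052, 0.79 | 0.049, 0.89 | 0.044, 0.80 | 0.074 |
| 0.7 | 0.049, 0.80 | 0.048, 0.85 | 0.046, 0.80 | 0.065 |

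The rule leaves the mean estimate unbiased. When baseline is flagged under no effect, the adjusted and unadjusted estimates differ on average by 0.28, 0.20 and 0.12 outcome SD for ρ = 0.3, 0.5 and 0.7. The planned effect in the same units is 0.50 × √(2(1 − ρ)) = 0.59, 0.50 and 0.39.

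4. **Baseline score as its own covariate.** With month T (0 or 1), group G and baseline Y0, the mean is b0 + b1T + b2G + b3GT + b4Y0 + b5Y0T. At T = 0 the response is Y0, and b0 = b2 = 0, b4 = 1 fits it exactly. In a simulated set of 140 CHOs the fit gave slope 1, group effect 0 and a month-0 residual variance of about 1e-31, against 0.88 at month 12. The month-0 variance goes to zero and the correlation between the two times is undefined, so the unstructured matrix cannot be estimated. The interaction coefficient (0.3068) equalled the ANCOVA group effect from month 12 alone.

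5. **Reporting only if significant.** SE = √(2 × 1.10 / 70) = 0.177, so only |d| above 1.96 × 0.177 = 0.35 would be reported. With μ = 0.50 / 0.177 = 2.82, the mean estimate given significance (the wrong-sign tail is negligible) is SE × [μ + φ(1.96 − μ) / Φ(μ − 1.96)] = 0.177 × (2.82 + 0.276 / 0.805) = 0.56, a ratio of 1.12. If the true d were 0.40, 0.30 or 0.20 the ratio would be 1.27, 1.58 or 2.23.

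**The case against.** Four arguments on the other side carry weight.

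- **A reader might infer that choosing covariates from the data inflates the primary type I error.** It does not when the rule is applied mechanically to the baseline score: step 3 gives 0.041 to 0.046, slightly conservative, with no bias. The excess appears only if the analyst is free to pick the model. What stands is that the missing list and threshold leave that freedom.
- **A reader might infer that the model is bound to fail whenever baseline scores differ.** The text speaks of patients, whose outcome is systolic BP. If that is what the outcomes means, the variable is not the aim 2a response and nothing degenerates there. The failure needs the outcomes to include the CHO adoption score. Even then the interaction coefficient stays meaningful as the ANCOVA effect, and the failed covariance fit would be noticed.
- **A reader might infer that always reporting the estimate would make a significant result less inflated.** It would not. The 12% is the usual consequence of conditioning on significance, and a significant result would show the same number after the change. Unconditional reporting restores an unselected set of estimates and gives a null result its interval.
- **The reporting clause may be meant mildly.** Its stated purpose is ease of interpretation, and with time coded 0 and 12 the raw coefficient is a change per month. The clause may only describe re-expressing that coefficient. The condition on significance is still explicit, and no other section removes it.

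**Conclusion.** The point holds as a flaw in how the primary analysis is fixed. It is not evidence that the planned test is invalid or the trial too small.

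- **Covariates:** the primary model stays undetermined until the arms have been compared, on a criterion unrelated to prognosis and worded for the wrong unit. The discretion is worth a type I error of about 0.065 to 0.077 at most between the two models simulated, for assumed correlations of 0.7 to 0.3. Using the rule in place of a fixed baseline adjustment also forgoes power: about 0.80 against 0.85 to 0.93.
- **Baseline score on both sides:** the covariance cannot be estimated if, and only if, the adoption score is among the variables added.
- **Conditional reporting:** this is the most certain defect, because it needs no assumption beyond the text. A null primary result would have no interval. Across repeated trials the reported estimates would average about 1.12 times the truth at d = 0.50, and more if the effect is smaller.

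Both rules should be changed before the primary analysis.

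**What to change.** 1. Delete the imbalance rule. Name the covariates in advance on prognostic grounds, at the level of the CHO or compound, and use the same set whatever the baseline table shows.
2. Use baseline adoption once: either as a response with the two arms' baseline means set equal, or as a covariate with month 12 as the only response.
3. Report the PF minus UC difference with its 95% CI whatever the p-value.
4. Add cohort or district only if randomisation was done within them. The trial status section says "The first cohort (18 CHPS zones) has been randomized and enrolled", and the setting covers three districts, but no section says that allocation was stratified by either.

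The cost is a change of wording and at most a few of the roughly 68 compound-level degrees of freedom (70 − 2). The target of 70 compounds does not change, and under the assumed correlations the baseline adjustment gains power.
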